### Plans to promote participant retention and complete follow-up {18b}

Study follow-up is performed at 4, 8 and 12 weeks with an outpatient clinic visit and CT scan. During these visits, all outcome measurements are performed by one of the researchers. To maximise participant retention, this study follow-up is parallel to the regular follow-up in the outpatient clinic by the treating physician (standard treatment). Also, we incorporate an extra telephonic interview after 2 weeks to monitor drug adherence and adverse events. Study treatment is limited to a maximum of 28 days and to a maximum of 56 capsules, regardless of whether a deviation from the study protocol occurs. In case of a protocol violation, study follow-up will remain unchanged.

### Data management {19}

Data management is described in the data management plan (DMP) which is available online [36].

### Confidentiality {27}

During the study, research data is pseudonymously collected in the electronic CRF (Castor EDC [37]). In every participating centre, a local key table is safely stored. This key table connects the research data to the patient data. The pseudonymous research data will only be shared after a data transfer agreement is signed. Research data is stored at the long-term storage facilities of the Academic Medical Center (Amsterdam, the Netherlands) for 15 years after completion of the study.

### Plans for collection, laboratory evaluation and storage of biological specimens for genetic or molecular analysis in this trial/future use {33}

Not applicable as no biological specimens are collected as part of this trial.

## Statistical methods

### Statistical methods for primary and secondary outcomes {20a}

Statistical analyses will be based on the intention-to-treat principle. Baseline assessments and outcome parameters will be summarised using simple descriptive statistics. Continuous, normally distributed variables will be expressed as means and standard deviations; continuous, non-normally distributed and ordinal variables as medians (25th–75th percentiles), and categorical variables as counts and percentages. Normality of data will be explored by a normal Q-Q plot and tested by the Shapiro-Wilk test. Where necessary we will use multiple imputations for handling missing data. In all analyses, statistical uncertainty will be expressed in two-sided 95% confidence intervals. A two-sided *p* value less than 0.05 is considered statistically significant. We will not correct for multiple testing.

The difference in the proportion of patients requiring surgery for cSDH within 12 weeks after the start of treatment will be analysed using Fisher’s exact test. In addition, logistic regression will be performed including treatment groups, stratification variables and baseline variables (if large differences exist between treatment groups) as independent variables. The effect size will be expressed in an adjusted odds ratio.

Differences in volume reduction of cSDH, neurological impairment (mNIHSS) and cognitive function (MOCA) between the treatment groups and overall time points will be analysed using a linear mixed model with treatment group membership as a fixed-effect and an appropriate random-effect structure. The number of falling incidents and mortality rate during the 12 weeks (and 6 months) follow-up will be analysed using Fisher’s exact test. ADL scores (Barthel Index and Lawton-Brody scale) and functional outcome score (mRS) at 12 weeks (and 6 months) will be compared with the two-sample *t*-test or Mann-Whitney test, where appropriate. Differences in the mean changes in the level of quality of life (SF-36) from baseline to 12 weeks (main secondary outcome) (and 6 months) will be analysed using the two-sample *t*-test. In addition, we will analyse these treatment effects by performing multivariable linear regression with treatment groups, the baseline values and the stratification variables as the independent variables.

For the cost-effectiveness analysis, the proportion of patients requiring surgery for cSDH within 12 weeks and 6 months after the start of treatment is the effect measure. The incremental cost-effectiveness ratio will be expressed as the costs per case of surgery avoided, as well as a cost-to-benefit ratio, where downstream costs associated with surgery and subsequent healthcare use until 12 weeks and 6 months are estimated. In addition, a cost-utility analysis (CUA) will evaluate cost differences in relation to differences in quality-adjusted life-years (QALYs). This CUA will estimate costs per QALY, to allow comparison with other health-related interventions or programmes. With a study horizon of 12 weeks and 6 months, no discounting will be applied.

We will differentiate between direct medical costs (surgical procedures, CT scans, pharmacological therapy, hospital stay, outpatient care, admissions to nursing home and other primary and paramedical health care following discharge), direct non-medical costs (travel to and from healthcare providers) and indirect costs (lost productivity due to absence from paid work). Healthcare utilisation during the index hospitalisation will be documented in the clinical report form. Healthcare and other resource use following discharge will be collected with the iMTA Medical Consumption questionnaire and the Productivity Costs Questionnaire [32] at 4, 8 and 12 weeks and 6 months. Unit costs for healthcare use will be estimated according to the Dutch guideline for economic evaluation research [38]. Medication costs will be valued by market prices [39]. Health-related QoL will be collected at 12 weeks and 6 months with the EQ-5D. Utility values for EQ-5D scores will be based on Dutch estimates [40]. Utility scores will be uniformly interpolated, assuming a constant health state between subsequent assessments.

Cost-effectiveness will be evaluated by calculating the incremental cost-effectiveness ratios (Δcosts/Δeffects). Robustness of the results for uncertainty in parameter estimates and assumptions will be evaluated in sensitivity analyses, including the UK valuation of health states.

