#### Current treatment

Currently, accepted treatment options are conservative and surgical. Conservative treatment consists of a wait-and-scan policy in which the patient is regularly monitored for neurological deterioration and growth of the haematoma on follow-up imaging. Anticoagulation and antiplatelet aggregation therapy is discontinued in low-risk patients, based on individual risk-benefit assessment and the discretion of the treating physician. In the Netherlands, about 50% of all cSDH patients is treated conservatively [7]. Spontaneous resolution of cSDH with a conservative treatment occurs in approximately 2.5% of patients however and is therefore relatively rare [8]. If the conservative treatment fails, surgical treatment has to be considered. In our own data (unpublished), 75% of the cSDH patients require surgery after a failed conservative treatment.

Surgical evacuation of the haematoma is currently the designated therapy in patients with severe symptoms or if the primary conservative treatment fails. Surgery usually consists of drainage of the liquefied haematoma through a burr hole craniostomy under general anaesthesia. This treatment is effective, but is also associated with life-threatening risks in these old, often frail, patients with multi-comorbidity. Postoperative complications such as a delirium and pneumonia can lead to a deterioration in cognitive functioning, loss of independency and even death. In a large series of 1205 patients, symptomatic recurrence after surgery was 9%, mortality 2% and unfavourable functional outcome 22% [9].

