## Trial design {8}

This multicentre study is designed as a double-blind, placebo-controlled, randomised, clinical superiority trial. Randomisation will be performed with a 1:1 allocation ratio.

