### Outcomes {12}

The primary endpoint is the number of patients requiring surgery for chronic subdural haematoma within 12 weeks after the start of treatment with the study medication.

Secondary endpoints are (1) number of patients requiring surgery within 6 months; (2) cSDH volume measured on non-contrast head CT (NCCT) with Brainlab Cranial Planning [24] at 4, 8 and 12 weeks; (3) neurological impairment (mNIHSS [25] score) at 4, 8 and 12 weeks; (4) number of falling incidents at 12 weeks; (5) cognitive functioning (Montreal Cognitive Assessment, MOCA score [26]) at 4, 8 and 12 weeks; (6) performance in activities of daily living (Barthel [27] and Lawton-Brody [28] score) at 12 weeks and 6 months; (7) functional outcome (modified Rankin Scale, mRS [29] score) at 12 weeks and 6 months; (8) quality of life (Short Form Health Survey, SF-36 [30] and five-dimensional EuroQol, EQ-5D-3L [31]) at 12 weeks and 6 months; (9) mortality at 12 weeks and 6 months; and (10) care and health-related costs (Medical Consumption Questionnaire, iMCQ [32] and Productivity Cost Questionnaire, iPCQ [32]) at 12 weeks.

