### Sample size {14}

In the Netherlands, approximately 50% of patients with cSDH is primarily treated conservatively [7]. Of these, 75% still need surgery (own data). Since oral TXA is an innovative treatment in these patients, little data is available concerning its efficacy. Until today, only five small studies, concerning a total of 39 patients treated with TXA, have been published [12–16]: none of these patients required surgery after the start of treatment. As this 100% reduction of surgery may well be an over-estimation of the true effect, a conservative estimate of 33% relative risk reduction was used in the sample size calculation (from 75% surgery in the placebo group to 50% surgery in the TXA group). A Fisher’s exact test with a 0.05 two-sided significance level will have 80% power to detect the difference between a control (placebo) group proportion of 0.75 and a treatment (TXA) group proportion of 0.50 when the sample size in each group is 64 (128 patients in total).

We consider the quality of life (QoL), measured with the SF-36, as an important secondary functional outcome indicator. With a sample size of 64 patients per treatment arm, we are also able to detect a Cohen’s *d* effect size (difference between the mean SF-36 scores of the control group and treatment group divided by the pooled SD) of 0.50. Although an effect size of *d* = 0.50 can be defined as ‘moderate’ [33], such a difference in mean QoL scores may be clinically important. Anticipating an attrition rate of about 8%, we will include 70 (64/0.92) patients in each group (140 patients in total).

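### The mixed model for cSDH volume has no rule for scans after surgery, so it mixes drug effect with drainage and can show equal or larger volume on TXA even if the drug works

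*Protocol article*

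**What the plan says.** Under Outcomes {12}, a secondary endpoint is "cSDH volume measured on non-contrast head CT (NCCT) with Brainlab Cranial Planning [24] at 4, 8 and 12 weeks". The retention section {18b} ties a CT scan to each of those visits and makes no exception for patients who have been operated on. Under Intervention description {11a}, surgery ends the study drug; nothing there ends follow-up or sets later scans aside.

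Statistical methods {20a} bases the analyses on intention-to-treat. Volume reduction, mNIHSS and MOCA are compared between the groups across the time points, and each "will be analysed using a linear mixed model with treatment group membership as a fixed-effect and an appropriate random-effect structure". No other fixed effect is named in that sentence. The paragraph closes, after the SF-36 analysis, with an additional regression on treatment, baseline values and stratification variables; whether this reaches volume is unclear.

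Two other statements bear on the model. The sample size assumes a fall "from 75% surgery in the placebo group to 50% surgery in the TXA group". The background section on current treatment says: "Surgery usually consists of drainage of the liquefied haematoma through a burr hole craniostomy under general anaesthesia".

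Sections {20b} and {20c} leave additional analyses, non-adherence and missing data to an SAP that was still unpublished.

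**The concern.** The primary-endpoint event acts directly on the secondary measurement. An evacuated haematoma is small because it was drained, whatever the patient was taking. By the plan's own assumption this happens 25 percentage points more often on placebo, during the period in which volume is measured. Followed as written, the model takes those scans as observed, and its treatment coefficient combines what TXA does to the haematoma with what surgery does.

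At stake is how the volume result is read. The Discussion says that the 4-, 8- and 12-week measurements are meant to follow the haematoma because the adequacy of the treatment length is unknown. A null or adverse volume result could be taken as evidence that TXA does not shrink haematomas, when it partly reflects fewer operations on TXA.

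**Working it through.** **The plan's own figure.** The plan gives no figure for the volume analysis, only for the primary endpoint: Fisher's exact test, where a "0.05 two-sided significance level will have 80% power" for 75% v 50% at 64 per group. Exact enumeration gives 80.2% power at 64 and 79.4% at 63, so 64 is reproduced. 64/0.92 = 69.6, rounded up to 70, also agrees. At 64 per arm the expected numbers operated on are 64 × 0.75 = 48 on placebo and 64 × 0.50 = 32 on TXA, which leaves 16 and 32 unoperated.

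**Mean volume when all scans count.** Let r be the post-operative residual and u the unoperated placebo volume, both as fractions of baseline, and let k be the proportional shrinkage of unoperated haematomas by TXA. With all surgery done before the scan:

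- placebo mean = 0.75r + 0.25u
- TXA mean = 0.50r + 0.50u(1 − k)
- TXA minus placebo = 0.25(u − r) − 0.5uk
- break-even k = 0.5(1 − r/u)

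Below the break-even k, TXA shows the larger mean volume. The surgery rates come from the plan; r, u and k are assumptions.

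| | r = 0.20 | r = 0.40 | r = 0.59 |
|---|---|---|---|
| Difference if k = 0, u = 1.0 | +0.20 | +0.15 | +0.10 |
| Break-even k, u = 1.0 | 0.40 | 0.30 | 0.205 |
| Break-even k, u = 0.8 | 0.375 | 0.25 | 0.13 |

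The upper end of r comes from the only residual figure in the document, a pilot study of 14 patients on TXA: a 41% reduction after surgery leaves 0.59, and a further 91% reduction of that by 90 days leaves 0.59 × 0.09 = 0.05. The background puts spontaneous resolution at about 2.5%. That suggests that u may stay high but does not give u.

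**In millilitres (assumed volumes).** Operated 15, unoperated placebo 60, unoperated TXA 45:

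- placebo 0.75 × 15 + 0.25 × 60 = 26.25; TXA 0.50 × 15 + 0.50 × 45 = 30.0. TXA looks 3.75 mL worse although its unoperated haematomas are 15 mL smaller.
- Unoperated TXA at 37.5: 0.50 × 15 + 0.50 × 37.5 = 26.25, no difference.
- Unoperated TXA at 30: 7.5 + 15 = 22.5, so TXA looks 3.75 mL better.

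**Timing of surgery.** A simulation of 64 per arm with scans at 4, 8 and 12 weeks assumed baseline volume 80 mL (SD 25). With complete balanced data, the random-intercept treatment effect equals the comparison of patient means. The table shows the difference in volume reduction, TXA minus placebo, in mL; negative means TXA looks worse.

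| Surgery timing | r | k = 0 | 0.1 | 0.2 | 0.3 | 0.4 |
|---|---|---|---|---|---|---|
| Mostly before week 4 | 0.2 | −13.5 | −9.0 | −4.8 | −0.4 | +3.9 |
| Mostly before week 4 | 0.4 | −9.9 | −5.7 | −1.4 | +2.8 | +7.0 |
| Even over 12 weeks | 0.2 | −10.7 | −5.8 | −0.6 | +4.4 | +9.7 |
| Even over 12 weeks | 0.4 | −8.0 | −3.1 | +2.1 | +7.1 | +12.4 |

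In the first row, a significant result in the wrong direction occurs in 79%, 50%, 19%, 4% and 0.1% of trials. Adding baseline volume leaves the estimate in place (for example −9.1 v −9.0 mL at k = 0.1).

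**Precision.** For baseline–follow-up correlation ρ and equal variances, the variance with baseline adjustment relative to an unadjusted change score is (1 − ρ²)/[2(1 − ρ)] = (1 + ρ)/2. That is 0.75 at ρ = 0.5 and 0.85 at ρ = 0.7, or 25% and 15% less variance.

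**The case against.** Keeping every scan under intention-to-treat is a legitimate treatment-policy comparison: it answers a different question and is not an error. That stands, and it is why the all-scan model can stay if it is labelled for what it estimates. It is also fair that the SAP may set a rule. However, the article itself fixes the main volume analysis, and a scan after surgery is neither missing data nor non-adherence, the topics that {20c} defers.

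Several stronger readings are tempting, and the document does not support them:

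- *The plan states that post-operative scans count like any other.* It does not. This follows from intention-to-treat, the fixed scan schedule and the absence of a rule.
- *The analysis ignores baseline altogether.* The outcome is a reduction, hence a change from baseline; the comparison runs across time points; and the closing regression sentence may apply. What can be said is that treatment is the only fixed effect named for the mixed model. A variance saving of 1 − ρ² would apply against an unadjusted final value, not against a change score.
- *The result is certain to go against TXA, and more so the better TXA works.* Preventing more operations widens the gap, but stronger shrinkage of unoperated haematomas offsets it. If u falls below r, the pull towards placebo disappears.
- *mNIHSS is distorted in the same direction.* Surgery may relieve symptoms, but the background also says that its complications can worsen cognition and independence. The direction for mNIHSS and MOCA is not established.

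**Conclusion.** The point holds in a conditional form. The volume analysis as written has no rule for surgery, and at the planned 75% v 50% it mixes drug effect with drainage. If unoperated haematomas stay larger than post-operative residuals, the comparison is pulled towards placebo. With u = 1 and r from 0.20 to 0.59, TXA looks worse unless k exceeds 0.40 down to 0.205; with surgery spread evenly over the 12 weeks, the sign turns at smaller k (about 0.2 for r = 0.2, between 0.1 and 0.2 for r = 0.4). All of r, u, k, baseline volume and surgery timing are assumptions, because the document gives none of them for this trial.

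This should be settled before unblinding, but it is not critical. Volume is one of ten secondary endpoints, SF-36 is named the main secondary outcome, and neither the primary analysis nor the sample size is touched.

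**What to change.** 1. Keep the all-scan mixed model, label it as the treatment-policy result that includes the effect of surgery, and state that it is not to be read as the drug's effect on the haematoma.
2. Pre-specify beside it a surgery-aware volume analysis: a mixed model that uses scans up to surgery only, with its missing-at-random assumption stated. As a sensitivity analysis, add a rank composite at 12 weeks with operated patients placed worst and the others ranked by volume.
3. Fit the mixed models with baseline value, visit, treatment-by-visit and the anticoagulant/antiplatelet stratum as fixed effects. This is for precision and does not replace step 2.
4. State how surgery is handled for mNIHSS and MOCA as well, without presuming a direction.

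The cost is SAP wording and one or two extra secondary analyses. The surgery date must be available; Data collection {18a} mentions only whether surgery took place. Neither added analysis is clean. Scans up to surgery are sparser, a patient operated on before week 4 contributes no follow-up scan, and surgery is reconsidered for progressive or non-resolving haematomas, so missing at random is doubtful. The rank composite ties 50% to 75% of patients in an arm at the bottom and largely repeats the primary endpoint, hence its place as a sensitivity analysis.

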## Data collection and management

### Plans for assessment and collection of outcomes {18a}

Research data is collected in an electronic CRF using Castor EDC (http://www.castoredc.com). Paper questionnaires are used for the SF-36, EQ-5D, iMCQ and iPCQ outcome measurements, which are filled in at home by the study participants themselves. These completed questionnaires are digitalised to Castor EDC by the investigators. During the outpatient clinic visit, the MOCA is assessed by the investigators using the official MOCA paper sheet, which is afterwards digitalised to Castor EDC by the investigators. The results of the mNIHSS, mRS, Barthel and Lawton-Brody are added to Castor EDC using direct entry during the outpatient clinic visit. Baseline patient characteristics, if a surgery for cSDH has been performed (primary outcome measurement), the number of falling incidents and mortality are registered in the medical records and added to Castor EDC after the outpatient clinic visit. Radiological data is also stored in the medical records; volume measurements are performed after the outpatient clinic visit and are then added to Castor EDC.

All outcome assessors are GCP licensed and are trained by the Principal Investigator in performing outcome measurements. The GCP certificates and training logs are stored in the Trial Master File. All electronic CRF entries are verified by checking the source data (paper questionnaires and medical records) which is done by the Principal Investigator or a delegated person.

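### Falls are defined as a count of incidents but assigned Fisher's exact test, which needs one categorical result per patient; endpoint and test do not match

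*Protocol article*

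**What the plan says.** Outcomes {12} lists ten secondary endpoints. The fourth is a count: "number of falling incidents at 12 weeks". Plans for assessment and collection of outcomes {18a} describes the data in the same way: "the number of falling incidents and mortality are registered in the medical records", from where they are entered in the electronic CRF.

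Statistical methods for primary and secondary outcomes {20a} then fixes the test, in one sentence shared with mortality: "The number of falling incidents and mortality rate during the 12 weeks (and 6 months) follow-up will be analysed using Fisher’s exact test".

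The primary endpoint is worded differently. Outcomes {12} says: "The primary endpoint is the number of patients requiring surgery for chronic subdural haematoma within 12 weeks". The methods section says: "The difference in the proportion of patients requiring surgery for cSDH within 12 weeks after the start of treatment will be analysed using Fisher’s exact". There the unit is plainly the patient.

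The article defers additional analyses, non-adherence and missing data to a later SAP. The test for falls is not deferred.

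**The concern.** A patient in this elderly population can fall more than once. Mortality gives one yes/no per patient and suits Fisher's exact test. A number of incidents does not: it has no natural denominator of patients, and falls in the same person are correlated.

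As written, the unit of analysis is open. It could be settled after the data are seen, and the choice changes both the false-positive rate and the power. Under either choice the test has no term for time at risk, which is shortened by death or withdrawal. At 6 months it also depends on whether the patient accepted the optional telephone interview.

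**Working it through.** **1. The article's own figure.** The only sample size is for the primary endpoint: Fisher's exact test, two-sided 0.05, 0.75 v 0.50, 64 per arm, 80% power (Sample size {14}). Full binomial enumeration gives 80.2% at 64 per arm and 78.3% at 62. Attrition: 64/0.92 = 69.6, so 70 per arm. Both figures reproduce. No fall rate or power is given for falls.

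**2. Assumptions for falls (not from the article).** Counts per patient are gamma-Poisson with mean m and variance m + k·m², where k is the dispersion; 64 per arm; two-sided 0.05; alternative is a halved fall rate.

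**3. Reading A: Fisher's test on incident totals out of 64.** The test in effect assumes variance m(1 − m) per patient. The true variance exceeds this by the factor

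R = (m + k·m²) / (m(1 − m)) = (1 + k·m) / (1 − m).

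The approximate true level is 2Φ(−1.96/√R).

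- m = 0.2, k = 0.5: R = 1.1/0.8 = 1.375; 1.96/√1.375 = 1.67; level about 9%.
- m = 0.5, k = 2: R = 2/0.5 = 4; 1.96/2 = 0.98; level about 33%.
- m = 0.6, k = 2: R = 2.2/0.4 = 5.5; 1.96/√5.5 = 0.84; level about 40%.

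This ignores Fisher's conservatism, so it runs a little high. Simulation over m = 0.2 to 0.6 and k = 0.5 to 2 gives 6% to 38%. If incidents in an arm exceed its number of patients, the table cannot be formed at all.

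**4. Reading B: Fisher's test on patients with at least one fall.** The probability of any fall is 1 − (1 + k·m)^(−1/k). With k = 1:

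- m = 0.6: 1 − 1/1.6 = 0.375
- m = 0.3: 1 − 1/1.3 = 0.231

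At m = 0.6 an arm expects 64 × 0.6 = 38.4 falls but only 64 × 0.375 = 24 fallers, so about 14 repeat falls are discarded.

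**5. The readings against a count analysis.** Simulation, 4,000 trials per setting, in %. The count analysis is a rate ratio with robust variance.

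| Control mean, k | Totals: null level | Any fall: null level | Any fall: power | Count: null level | Count: power |
|---|---|---|---|---|---|
| 0.3, 1 | 11 | 3 | 23 | 5 | 35 |
| 0.3, 2 | 15 | 3 | 19 | 6 | 31 |
| 0.5, 1 | 21 | 3 | 31 | 6 | 50 |
| 0.5, 2 | 29 | 3 | 24 | 6 | 44 |

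**6. Power at matched level.** Part of the power gap arises because Fisher's test runs at about 3%. Holding negative binomial regression to Fisher's actual level (1,500 trials per setting):

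| Control mean, k | Fisher, any fall | Count model, nominal | Count model, matched level |
|---|---|---|---|
| 0.6, 0.5 | 44% | 63% | 58% |
| 0.3, 1 | 24% | 33% | 24% |
| 0.2, 1 | 16% | 23% | 18% |

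The gaps shrink from 19, 9 and 7 points to 14, 0 and 2. Over the whole assumed range, with a robust count model, the gain is about 7 to 24 points nominally and about 0 to 15 at matched level.

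**7. Time at risk.** The article expects about 8% attrition, measures mortality and makes the 6-month contact optional. Fisher's test has no exposure term. No size is put on this here.

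**The case against.** The strongest reply is that the sentence simply means patients with at least one fall. Falls share it with mortality, which is binary, and Fisher's test would be an odd choice for anything else. On that reading the test is valid, with a null level of about 3% to 4%, and preferring a count model is a matter of efficiency. This is plausible and largely stands. It does not remove the mismatch. Where the article means patients it says patients, both the definition and the data collection speak of incidents, and no section defines a faller.

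A reader might infer that Fisher's test is simply unusable for falls, or that the trial will overstate its evidence. The article supports neither. The test works once falls are reduced to yes/no. The inflated error belongs to incident totals, a reading that the text leaves open but does not specifically endorse.

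A reader might also take a large power loss as established. With 0.6 v 0.3 falls and k = 1, for example, Fisher's test has 35% power against 58% for negative binomial regression. That is one assumed scenario, and it compares tests whose actual levels are 3.2% and 6.6%. Falls are taken from medical records, so the recorded rate may be lower, and at low rates the matched-level gain can vanish.

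Multiple imputation, planned where necessary, may help with missing follow-up. It does not adjust for exposure or for death. Unequal follow-up is in any case a lesser issue at 12 weeks than at 6 months.

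**Conclusion.** The mismatch is real and lies in what the article states, so it is not detail left to the SAP. What follows from it depends on the reading: an inflated false-positive rate on incident totals, or a valid test of a different endpoint on patients with at least one fall, usually with less power than a count model. All the sizes rest on assumed fall rates, gamma-Poisson counts and 64 per arm; the power figures also assume a halved rate.

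The importance is limited. Falls are one of ten secondary endpoints and not the main one, which is SF-36. Neither the primary analysis nor the sample size is touched. The point should be corrected before unblinding, but the trial's main conclusion does not depend on it.

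**What to change.** State the unit of analysis before unblinding, in one of two ways.

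- **Preferred: keep the count.** Analyse falls per patient by negative binomial regression, or by Poisson regression with robust variance. Include treatment, the anticoagulant/antiplatelet stratum and log follow-up time as offset, and report a rate ratio with 95% CI. Give the proportion with at least one fall, with Fisher's test, as a supportive result.
- **Minimal: keep the test.** Reword the endpoint in Outcomes {12} as patients with at least one fall, and accept that repeat falls are not used.

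In the same edit, settle the time point: Outcomes {12} lists falls at 12 weeks only, while the methods sentence adds 6 months.

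The cost is wording only, since incidents are already recorded. One downside is that model-based p values can be slightly liberal at 64 per arm (6.6% for negative binomial in the scenario with mean 0.6 and k = 1). Robust variance held the level at 5.0% there. A permutation test of mean falls also controls it (3.2%), but gives back some power: 50% against 58% for robust Poisson and 36% for Fisher's test on any fall in the same set of simulations.

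### Barthel, Lawton-Brody and mRS: the lead comparison is unadjusted, and it is unclear whether the added baseline-adjusted regression covers these scales

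*Protocol article*

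**What the plan says.** Outcomes {12} of the protocol article lists the Barthel, Lawton-Brody and mRS scores as secondary endpoints at 12 weeks and 6 months. Statistical methods {20a} treats them as follows.

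- The scores are compared by a "two-sample *t*-test or Mann-Whitney test, where appropriate". Neither the baseline score nor the stratum enters this comparison.
- The next sentence turns to SF-36, named as the main secondary outcome, and gives it a two-sample t-test on change.
- Then follows: "In addition, we will analyse these treatment effects by performing multivariable linear regression with treatment groups, the baseline values and the stratification variables". The text does not say whether this refers back to SF-36 alone or also to the ADL scores and mRS.
- Earlier in the section, ordinal variables are to be described by medians and quartiles, and "Normality of data will be explored by a normal Q-Q plot and tested by the Shapiro-Wilk test".
- On missing data: "Where necessary we will use multiple imputations for handling missing data". Section {20c} leaves the detail to an SAP that is not shown.

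Sequence generation {16a} gives one stratification factor, anticoagulant and/or antiplatelet use. Sample size {14} gives no power for these three scales.

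**The concern.** Barthel, Lawton-Brody and mRS are ordinal scales. The plan describes ordinal variables by medians, yet it leaves open whether their treatment effect is a difference in means or a comparison of ranks. It also does not say which result leads if the unadjusted test and the regression disagree. On the wide reading there are 3 scales × 2 time points × 2 analyses = 12 tests, with no correction for multiplicity.

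The more practical issue is adjustment. Pre-treatment function may predict later function strongly in this population. If it does, an unadjusted test discards information that the plan itself expects to use in its regression. On the narrow reading of the regression sentence, these scales get no adjusted analysis at all.

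These scales matter to the trial's argument. Objectives {7} expects that avoiding surgery will prevent loss of independence, and the Discussion expects an answer on functional outcome.

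**Working it through.** **1. The plan's own figures.** From Sample size {14}: 0.75 v 0.50, Fisher's exact test, two-sided 0.05, 64 per arm. Exact enumeration gives 80.2% power at 64 per arm and 79.4% at 63, so 64 is reproduced. For SF-36 at d = 0.50 and 64 per arm, the t-test has 80.1% power. Attrition: 64/0.92 = 69.57, rounded up to 70 per arm, 140 in total. The point made here changes none of these.

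**2. What baseline adjustment is worth on a continuous scale.** Adjustment multiplies the residual SD by √(1 − ρ²), where ρ is the correlation between baseline and follow-up. By the normal approximation, power = Φ( d / [√(1 − ρ²) · √(2/n)] − 1.96 ). The documents give no ρ, so it is an assumption. The d = 0.50 is borrowed from the SF-36 statement for illustration, with n = 64.

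- Unadjusted: 0.50/√(2/64) = 2.828; 2.828 − 1.96 = 0.868; power 80.7%.
- ρ = 0.6: √(1 − 0.36) = 0.8; 2.828/0.8 = 3.535; 3.535 − 1.96 = 1.575; power 94.2%.

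| ρ | Power at 64 per arm | n per arm for 80% |
|---|---|---|
| 0 (unadjusted) | 80.7% | 63 |
| 0.3 | 84.3% | 58 |
| 0.4 | 87.0% | 53 |
| 0.5 | 90.4% | 48 |
| 0.6 | 94.2% | 41 |
| 0.7 | 97.7% | 33 |

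**3. The same question on an ordinal scale.** Assumed inputs: seven levels with control proportions 15/21/21/19/14/5/5%, death as the worst level (5%), a latent logistic model, baseline effect 1.3 per SD, conditional common odds ratio 2.2, 64 per arm. Three separate runs, power in each:

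| Analysis | Run A (800 replicates) | Run B (400 replicates) | Run C |
|---|---|---|---|
| t-test | 50% | 51% | 51% |
| Mann-Whitney | 50% | 51% | 53% |
| Linear regression with baseline | not run | 66% | 65% |
| Proportional odds with baseline | 66% | 70% | 67% |

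The Monte Carlo standard error is about √(0.5 × 0.5/800) = 1.8 points in run A and √(0.5 × 0.5/400) = 2.5 points in run B. In run C, adding baseline to the t-test gains 65 − 51 = 14 points. Moving from the linear to the ordinal model gains 67 − 65 = 2 more.

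**4. A weaker baseline.** With the effect cut to 0.6 per SD, Mann-Whitney had 67%, adjusted linear regression 69% and proportional odds 73%. Another run with a weaker baseline put all four analyses between 70% and 75%.

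**5. A second model as a cross-check.** Assumed: mRS levels 0 to 5 plus death as worst, common odds ratio 2.0, correlated latent normals, 3,000 runs.

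| Analysis (deaths included) | ρ = 0.6 | ρ = 0.3 |
|---|---|---|
| Mann-Whitney, unadjusted | 60% | 59% |
| Linear regression with baseline | 72% | 60% |
| Rank regression with baseline | 74% | 62% |

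Under no effect, rejection was between 4.4% and 4.9% for every analysis tried. Shapiro-Wilk rejected normality in essentially every run, so a rule built on it would always have led to Mann-Whitney.

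**The case against.** The strongest reply is that the same section already adds a regression on baseline and stratum, so the power is not lost. Most of this stands. If that regression covers these scales, it recovers nearly all of the gain (65 or 66% against 67 or 70% for proportional odds). Setting an unadjusted test against a proportional-odds model shows only half of the plan. What remains is that the regression is secondary to the unadjusted test and its scope is ambiguous.

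It is also fair to say that the size rests on assumed inputs, that a weakly prognostic baseline leaves little to gain, and that these are secondary outcomes.

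Two stronger readings are tempting and should not be drawn:

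- **Deaths.** A reader might infer that patients who died are dropped or given imputed living scores. The article says neither. Its imputation sentence does not mention death, mortality is tested separately, and {20c} defers missing-data methods to the SAP. The question is worth confirming, because comparing survivors only can mislead if deaths differ between arms. The power effect alone is modest: 60% with deaths ranked worst against 54% with deaths dropped, at 5% assumed control mortality in the second model. Ranking death worst is also a choice of estimand, and not simply a correction.
- **The normality check.** A reader might infer that Shapiro-Wilk picks the test and distorts the error rate. The check stands beside the rules for descriptive summaries, and its link to the choice of test is not stated. "two-sample *t*-test or Mann-Whitney test, where appropriate" could simply mean by type of scale. The simulations show no inflation of type I error.

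**Conclusion.** The point holds as an improvement to the analysis. The lead comparison for three ordinal scales ignores baseline and stratum, the effect measure is left between a mean and a rank comparison, and the scope of the adjusted regression is unclear. Under assumed inputs, leading unadjusted means about 50% power against 65 to 67% when baseline is strongly prognostic, and little or no difference when it is weak. Nearly all of that comes from adjustment; the ordinal form adds a few points at most and fits the scale better.

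The loss is full only if the regression is confined to SF-36. If it covers these scales, what is left is mainly a matter of naming the lead analysis. This rests on an assumed prognostic strength, an assumed score distribution and an assumed effect. It also rests on baseline scores being collected: the regression sentence implies baseline values, but the endpoint list gives only follow-up times and the timeline figure is not shown. The primary analysis and the 140-patient sample size stand as they are.

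**What to change.** For each of Barthel, Lawton-Brody and mRS, at 12 weeks and 6 months, name one lead analysis in advance: a proportional-odds regression on treatment, the baseline score (if collected) and the anticoagulant/antiplatelet stratum. Report the common odds ratio with its 95% CI and keep Mann-Whitney as a supporting test. State whether the existing linear-regression sentence applies to these scales or only to SF-36. Confirm in the SAP how a patient who died enters each score.

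The cost is wording in the protocol and SAP, with no new data if baseline scores are already collected. There is a small downside: a common odds ratio is less familiar to clinical readers than a mean difference, and the proportionality assumption needs a check.
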